**Figure 2 figure2:**
[figure not shown]
Points for transcutaneous electrical nerve stimulation (TENS) electrodes placed on.

**Figure 3 figure3:**
[figure not shown]
Points for auricular seed acupressure.

**Figure 4 figure4:**
[figure not shown]
Points for acupressure during the latent phase of labor.

**Figure 5 figure5:**
[figure not shown]
Points for acupressure during the active phase of labor.

### Ethical Considerations

This study has been approved by the Ethics Committee of the Obstetrics and Gynecology Hospital of Fudan University (OGHEC2023-21). The Data Safety Monitoring Committee will conduct continuous safety monitoring of the project implementation and perform annual ethical reviews to ensure procedural coherence. The Data Management and Quality Control Committee will execute quality control evaluations at the initial, intermediate, and preconclusion phases of the project, with a preliminary analysis performed at the midterm stage to guarantee the high-quality execution of the study.

The trial was prospectively registered in the Chinese Clinical Trial Registry on March 23, 2023 (ChiCTR2300069705). All data will be kept confidential, with access restricted to the researchers. Before enrollment, all participants will provide informed consent and will be fully informed of their right to withdraw from the study at any time. Participating women are explicitly assured that their personal data will be managed under strict confidentiality protocols within the research group. All collected study materials will undergo deidentified processing to ensure complete anonymization.

### Blinding

A double-blind design is not feasible in this study due to the necessity for participants to provide informed consent regarding the pain relief methods administered. However, several measures are implemented to minimize potential bias. Midwives delivering the interventions will not be involved in outcome assessment or data analysis, thereby reducing both performance and detection bias. A standardized protocol will be established to ensure consistent delivery of interventions and uniformity in data collection. To minimize measurement bias, outcome assessors will be blinded to the group allocation, and participants will be instructed not to disclose which treatment intervention they receive. Data collectors, who will be independent of the intervention process, do not have access to any information regarding the intervention groups. In addition, statisticians conducting the data analysis will be blinded to group allocation and will not have access to the intervention details. Analyses will be performed according to a prespecified plan to prevent selective reporting. Regular monitoring of adherence to the protocol across the LDUs will be conducted to ensure consistency and reduce the risk of bias. To further enhance the validity and objectivity of the findings, data analysis will be independently verified by a third party to minimize any potential bias.

### Outcome Measures

The primary outcome of this trial is pain perception, measured using the visual analog scale (VAS). Pain perception was assessed from the onset of labor pain, with evaluations recorded every 30 minutes until pharmacological pain relief was administered or delivery occurred. VAS scores ranged from 0 (no pain) to 10 (extreme pain). Secondary outcomes included the interval from the NPI, the rate of epidural analgesia, mode of delivery, the amount of postpartum bleeding within 2 hours, neonatal Apgar scores at 1 and 5 min, labor duration, perineal tear rates, and the overall childbirth experience. The Chinese version of the Childbirth Experience Questionnaire (CEQ) [31] was used to evaluate women’s overall childbirth experience. All secondary outcomes, with the exception of the childbirth experience, assessed post delivery using the CEQ, will be extracted from electronic medical records by the research team, who will not be involved in providing care.

In addition, a purposive sampling method will be used to recruit women from each group for semistructured interviews. The interviews will primarily focus on women’s perceptions and experiences of nonpharmacological pain relief methods during childbirth. The number of women to be interviewed will not be predetermined. Interviews will continue until data saturation is reached, which is the point at which no new information or themes are detected in additional data [32].

### Statistical Analysis

Data will be entered into the database after verification by 2 independent researchers. Quantitative data will be analyzed using SPSS 26.0 statistical software (IBM Corp), following an intention-to-treat (ITT) approach. Normally distributed continuous variables are presented as mean (SD), while non-normally distributed continuous variables are expressed as median (25th percentile-75th percentile). Categorical data are described using frequencies and percentages. Comparisons of normally distributed continuous variables were conducted using ANOVA or the Kruskal-Wallis test, while *t* tests were used for intergroup comparisons. A significance level of *P*<.05 is deemed statistically significant. Missing data will be addressed using multiple imputations.

Qualitative data will be analyzed using NVivo 14 software (Lumivero) through content analysis. Interview materials will be coded and categorized based on key themes derived from the interview guide. Perspectives on similar topics will be grouped and synthesized. Following coding, the software’s classification extraction function will be used to retrieve relevant content from all files under specific codes, allowing for comparison and linkage of different coded content, and identification of primary and secondary viewpoints based on frequency of occurrence for further analysis.

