**Methods:**

This is a 12-month stepped wedge cluster randomized trial to be conducted in 4 labor and delivery units (LDUs) at the Obstetrics and Gynecology Hospital of Fudan University. Each unit will implement 4 types of interventions: TENS, acupoint stimulation, TENS combined with acupoint stimulation, and a control group. We aim to recruit approximately 588 pregnant women. The project will be evaluated using both quantitative and qualitative data. Quantitative data will include visual analog scale (VAS) scores, the nonpharmacological to pharmacological pain management interval (NPI), the rate of epidural analgesia, and childbirth outcomes. Qualitative data will include interviews with the women and midwives.

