## Methods

### Trial Design

This 12-month exploratory SWCRCT will be conducted at the Obstetrics and Gynecology Hospital of Fudan University in Shanghai, China—a specialized tertiary hospital that manages approximately 10,000 births annually across its 2 campuses. The study involves 4 parallel groups, assigned in a 1:1 ratio, each receiving 1 of 4 interventions: TENS, acupoint stimulation, a combination of TENS and acupoint stimulation, or control measures. Randomization is performed at the cluster level using computer-generated sequences to determine the staggered initiation order of interventions across 4 labor and delivery units (LDUs; LDU1, LDU2, LDU3, and LDU4). Each LDU will be assigned to deliver a single intervention for a 3-month period, followed by a transition to the next phase according to the predetermined sequence. This design ensures that each 3-month cohort will comprise unique participants, eliminating crossover exposure to multiple interventions. Participants will be selected based on predefined criteria and confirmed for inclusion before the initiation of the interventions. Figure 1 shows the overall study flow. Recruitment began on April 1, 2023, and all interventions were completed by March 29, 2024, aligning with the 12-month study window. This protocol adheres to the SPIRIT (Standard Protocol Items: Recommendations for Interventional Trials) 2013 checklist [29].

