### Sample Size

The sample size calculation is conducted using the formula for SWCRCTs as outlined by Hemming and Taljaard [30]. The design effect (DE) was calculated based on the meta-analysis by Johnson et al [14], which suggests that a reduction exceeding 0.7 in VAS pain scores indicates a clinically significant effect of TENS. Assuming an expected effect size of 0.7, an intraclass correlation coefficient (ICC) of 0.01, and an estimated sample size of 117 participants in each intervention group, the DE is determined to be 2.16. The total sample size is then estimated using a significance level of 0.05 and a power of 0.8, resulting in 132 participants per group. After accounting for a 10% dropout rate, the required sample size is adjusted to 147 participants per group, culminating in a total of 588 participants. This calculation is verified using PASS 15.0 software (NCSS), which confirms a power of 0.89, thus ensuring the study’s adequacy.

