### Randomization and Allocation

This study uses a SWCRCT design, wherein the interventions are allocated at the cluster level, specifically based on the LDUs, rather than at the individual participant level. The randomization process is conducted by a researcher not involved in the intervention using a computer-generated random number list to determine the sequence of interventions across the 4 LDUs. The random allocation sequence is subsequently sealed in opaque envelopes, each corresponding to a specific LDU. This allocation sequence will be disclosed to the midwives in each cluster at the appropriate time. The midwives, trained to implement the intervention, will execute it according to the allocated sequence. This approach ensures allocation concealment and mitigates the risk of selection bias.

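### The named tests (ANOVA or Kruskal-Wallis, then t tests) treat women as independent although interventions were allocated by LDU in 3-month blocks, so the 5% error rate of the primary comparison is not secured

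*Protocol article*

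**What the plan says.** Four parts of the protocol article bear on this.

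- **Allocation** (Randomization and Allocation): "the interventions are allocated at the cluster level, specifically based on the LDUs, rather than at the individual participant level". A random number list is used "to determine the sequence of interventions across the 4 LDUs".
- **Layout** (Trial Design): "Each LDU will be assigned to deliver a single intervention for a 3-month period, followed by a transition to the next phase". The abstract adds: "Each unit will implement 4 types of interventions: TENS, acupoint stimulation, TENS combined with acupoint stimulation, and a control group". Four LDUs over four quarters give 16 LDU-period cells.
- **Sample size**: the calculation assumes "an intraclass correlation coefficient (ICC) of 0.01" and a design effect of 2.16, and arrives at 588 women.
- **Analysis** (Statistical Analysis): "Comparisons of normally distributed continuous variables were conducted using ANOVA or the Kruskal-Wallis test". t tests are used between groups, and P<.05 is the threshold.

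The article names no LDU effect, period effect, mixed model, GEE, cluster-robust variance or small-sample correction. The Blinding section refers to a prespecified plan but describes no method.

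**The concern.** The article does not merely leave the model to a later document. It names the tests, and those tests conflict with its own allocation scheme and its own sample-size reasoning. Clustering was judged large enough to multiply the sample by 2.16, yet it is absent from the test.

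Two separate problems follow.

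1. **Correlation.** Women delivering in the same LDU in the same quarter share staff and local practice. If cells differ beyond sampling error, a test based only on between-woman variation misjudges the uncertainty of an arm difference.
2. **Calendar time.** The article does not say that the sequences were constrained so that each intervention appears once in every quarter. If they were not, any drift in VAS over the 12 months leaks into the arm comparison, and nothing in the named tests removes it.

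At stake is whether a VAS result at P<.05, for the hypothesis that the combination beats standard care, carries the error rate it claims.

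**Working it through.** **Inputs from the article.** 4 LDUs, 4 periods of 3 months, 147 women per group, 588 in total, ICC 0.01, 117 per group used in the design effect, alpha 0.05 (taken as two-sided), effect 0.7 VAS points.

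**Assumed, because the text does not give them.** CAC from 0 to 1; drift of 0.1 or 0.2 VAS points per quarter; SD of 1.38 or 2.0.

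**1. The plan's own figures.** DE = 1 + (m − 1) × ICC = 1 + 116 × 0.01 = 2.16, which reproduces. 132 / 0.9 = 146.7, so 147, and 4 × 147 = 588, which also reproduces. This DE is the parallel-cluster form, with all 117 women of an arm in one cluster.

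**2. What that DE would imply.** The real error rate of an unadjusted 5% test is 2 × (1 − Φ(1.96 / √DE)). With DE 2.16, √DE = 1.47 and the rate is 18.2%. It does not describe a layout in which each LDU delivers every intervention.

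**3. Balanced 4 × 4 layout.** Women per cell: m = 147 / 4 = 36.75. For a two-arm comparison, DE = 1 + (m − 1) × ICC − m × CAC × ICC. The ANOVA column comes from simulating 16 cells of 37 women with no treatment effect (4,000 to 8,000 runs per scenario). Simulated t-test rates agree with the formula.

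| CAC | DE | t test, type I error | Global ANOVA, type I error |
|---|---|---|---|
| 0 | 1.357 | 9.3% | 12-13% |
| 0.5 | 1.174 | 7.0% | about 9% |
| 0.8 | 1.063 | 5.7% | 6-7% |
| 1 | 0.990 | 4.9% | about 5% |

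**4. SD for the drift scenarios.** No SD is stated. Solving back from 132 per group: 132 / 2.16 = 61.1 effective women per arm, so SD = 0.7 × √(61.1 / 2) / (1.96 + 0.84) ≈ 1.38.

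**5. Sequences not balanced over time.** Each LDU's order is drawn at random without a balance constraint; ICC 0.01, CAC 0.8.

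| SD | Drift per quarter | t test | Global ANOVA |
|---|---|---|---|
| 1.38 | 0.1 | about 9% | 12-14% |
| 1.38 | 0.2 | 19-20% | about 34% |
| 2.0 | 0.2 | about 13% | about 20% |

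**6. The alternative.** An additive analysis of the 16 cell means has 16 − 1 − 3 − 3 − 3 = 6 residual df. In simulation its type I error stays at about 4% to 6%.

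**The case against.** The strongest defence is that the damage may be small. If every LDU gives each arm once, the sequences balance over quarters and LDU differences are stable, the t test runs at 4.9%, marginally conservative. With equal cells, the raw difference in arm means then equals the LDU-adjusted one, so the within-LDU comparison is not lost from the estimate. The article is also condensed, cites a plan that is not shown, and does not say that the ANOVA is one-way. All of this stands as a limit on size. It does not rescue the t tests, which have no place for LDU or period, and the text does not establish the favourable conditions. The study flowchart, which was not available for this review, may show the sequences.

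Several stronger readings are tempting and are not supported:

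- **That the false-positive rate is 18%.** This follows only from the parallel-cluster DE, not from the 16-cell layout.
- **That standard errors are always too small.** Direction and size depend on CAC and on the layout, as the near-nominal case shows.
- **That the period was a unit of randomization.** The LDU's sequence was randomized. The period is the step of the design, although it still belongs in the model.
- **That the plan's confidence intervals are wrong.** The section mentions none. Any interval built on the same standard error would share the fault, but that is an inference.

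**Conclusion.** The point holds: the stated tests conflict with the allocation and with the sample-size reasoning, and the nominal 5% level is not secured. This is an error in what is written, not a missing detail.

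Its size is moderate at the plan's own ICC. With balanced sequences it is about 5% to 9-10% for combination versus control and about 5% to 13% for the global test, depending on CAC. It becomes serious if sequences are unbalanced and VAS drifts: about 9-19% and 12-34% respectively at SD 1.38. At SD 2.0 with 0.2 points of drift per quarter, the figures are about 13% and 20%. CAC, drift and SD are assumptions, so certainty about the conflict is high and certainty about its magnitude is limited. Nothing here shows that the trial's eventual result is wrong. It shows that the named tests cannot vouch for it.

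**What to change.** Replace the ANOVA and t-test sentence with a cluster-period analysis:

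- A linear mixed model with effects for intervention (4 levels), LDU (4) and period (4), a random LDU-by-period effect, and small-sample degrees of freedom (Satterthwaite or Kenward-Roger). An additive analysis of the 16 LDU-period means on 6 residual df is an acceptable alternative.
- Apply it to one prespecified VAS summary per woman. If the 30-minute scores are modelled directly, add a woman-level random effect; otherwise correlation within a woman is left out.
- Use the same LDU and period terms for binary outcomes such as epidural use.
- Report combination minus control with its 95% CI, and print the sequence each LDU actually followed.

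The Results section says data collection is complete and analysis is in progress, so the change cannot be presented as made before the data were available. Date it, disclose it, and say what had been seen by then.

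The cost is analysis time and precision. No new data are needed, and the mixed-model procedures in SPSS can fit the model. The critical value on 6 df is about 2.45 instead of 1.96, so at an equal standard error the interval is 2.45 / 1.96 = 1.25 times as wide.

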## Results

The study commenced on April 1, 2023, and as of March 29, 2024, a total of 600 eligible participants have been enrolled, surpassing the initial target of 588. Data collection has been completed, including quantitative assessments of labor pain intensity, analgesic use, and childbirth outcomes, alongside qualitative interviews with participating women. Currently, data analysis is in progress, with preliminary findings anticipated to be available by March 2025. We hypothesize that TENS combined with acupoint stimulation will demonstrate greater efficacy in managing labor pain compared with standard care. This effect may be observed in key outcome measures, including the VAS score and enhanced maternal childbirth experience.

## Discussion

### Principal Findings

This study protocol outlines a SWCRCT designed to evaluate the effectiveness of TCM-based TENS and acupoint stimulation for labor pain management. By addressing the limitations of previous research, such as inconsistent implementation techniques and a lack of high-quality evidence [9,33], this study aims to generate robust and clinically relevant findings. We anticipate that the results will provide valuable insights into the potential of nonpharmacological methods to delay the use of pharmacological pain relief, particularly epidural analgesia, while also reducing associated risks such as intrapartum fever [34,35]. Furthermore, the introduction of the NPI as a novel outcome indicator is expected to offer a new perspective on evaluating the efficacy of nonpharmacological interventions. The mixed methods approach, incorporating both quantitative and qualitative data, will provide a comprehensive understanding of the interventions’ impact on labor pain management and women’s childbirth experiences.

### Comparison With Previous Work

This study builds on previous work by conducting a meta-analysis of 32 RCTs evaluating the use of TENS for labor pain relief [33]. The findings indicate that TENS can effectively reduce labor pain; however, the overall quality of the evidence was low, with significant heterogeneity across studies. This variability likely arises from individual differences among laboring women and inconsistencies in the implementation of TENS techniques.

Furthermore, previous studies have predominantly explored comparisons between nonpharmacological pain relief methods and pharmacological pain relief methods [1,36]. However, there is limited evidence on the sequential use of nonpharmacological interventions followed by pharmacological approaches, particularly in the context of delaying the administration of epidural analgesia.

Furthermore, several studies have demonstrated that nonpharmacological pain management can reduce the necessity for epidural analgesia [37] and that epidural analgesia is directly associated with an increased risk of intrapartum fever [34,35]. In light of this, we introduce a novel outcome indicator in this study: the NPI. Compared with the VAS, a subjective evaluation metric for assessing analgesic efficacy, the NPI provides an objective measure to evaluate how nonpharmacological pain management affects the use of epidural analgesia and the incidence of intrapartum fever. This study seeks to evaluate the effectiveness of TCM-based nonpharmacological pain relief methods in delaying and reducing the duration of epidural analgesia, thereby potentially lowering maternal fever rates and improving the quality of labor management.

We have also found that previous studies primarily focused on the effects of nonpharmacological pain relief measures during labor on quantitative health outcomes [19]. In contrast, the perceptions and experiences of women receiving labor pain management have been less thoroughly explored. This study aims to incorporate a mixed methods approach, supplementing the quantitative findings with experiential feedback from various stakeholders. This approach allows for a more comprehensive understanding of the effectiveness of TENS and acupoint stimulation in women undergoing a trial of labor.

### Limitations

However, the study has certain design limitations. First, participants are recruited from a single midwifery institution in Shanghai, which is a tertiary, university-affiliated women’s hospital. Consequently, factors such as geographical location and the level of medical and nursing care may limit the generalizability of our findings to the broader population. Future large-scale multicenter clinical studies will be necessary to further validate the effectiveness of acupoint stimulation and TENS technology for labor pain management in pregnant women from diverse regions and cultural backgrounds. In addition, labor pain intensity in this study was quantified using the VAS score, which carries inherent subjectivity. Finally, participants included in this study are low-risk pregnant women; thus, the applicability of TCM-based nonpharmacological pain relief methods for high-risk women undergoing a trial of labor remains to be further explored and validated.

### Future Directions

This study aims to provide robust evidence supporting the integration of TCM-based nonpharmacological pain relief techniques into routine maternity care. Future research should explore the feasibility of implementing these methods across various health care settings, including community hospitals and primary care centers. Furthermore, additional studies should assess the long-term effects of these pain relief techniques on maternal and neonatal outcomes, as well as their cost-effectiveness. It will also be essential to explore their applicability in high-risk pregnancies and diverse cultural contexts to inform the development of universal guidelines.

### Conclusion

This study protocol details the interventions of acupoint stimulation and TENS for women undergoing a trial of labor. The main objective of this SWCRCT is to determine the effects of acupoint stimulation combined with TENS in reducing labor pain, enhancing women’s childbirth experiences, and improving maternal-fetal health outcomes. In this study, we introduce a novel outcome indicator termed the nonpharmacological to pharmacological pain management interval (NPI), which monitors whether the application of nonpharmacological pain relief measures can delay or prevent the use of epidural analgesia. In addition, the integration of qualitative and quantitative methods will enrich the research on TENS and acupoint stimulation technology within the realm of nonpharmacological labor pain relief, providing high-quality evidence for the future establishment of industry standards and guidelines.

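### NPI has no observed value for women who deliver without pharmacological relief, and the stated continuous-outcome tests cannot make it show delay or prevention of epidural use

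*Protocol article*

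**What the plan says.** NPI is defined only through its name. The Conclusion of the protocol article gives its purpose as an indicator "which monitors whether the application of nonpharmacological pain relief measures can delay or prevent the use of epidural analgesia", and Comparison With Previous Work adds that "the NPI provides an objective measure to evaluate how nonpharmacological pain management affects the use of epidural analgesia".

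Outcome Measures lists it without a start event, a stop event or a rule for women who never reach the end point: "Secondary outcomes included the interval from the NPI, the rate of epidural analgesia, mode of delivery". The same section foresees such women, because pain scores are taken with "evaluations recorded every 30 minutes until pharmacological pain relief was administered or delivery occurred".

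Statistical Analysis gives the methods. "Comparisons of normally distributed continuous variables were conducted using ANOVA or the Kruskal-Wallis test", with t tests between groups, under intention to treat. It adds: "Missing data will be addressed using multiple imputations". No time-to-event or competing-event method is named, and NPI is not exempted from imputation.

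Trial Design calls the fourth arm control measures, and Results calls the comparator standard care. Table 1 describes only the three active techniques.

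**The concern.** The outcome and the tests do not fit each other. A woman who delivers without pharmacological relief is exactly the prevention case, and she has no interval to enter into an ANOVA or a t test. Two routes are open under the stated methods:

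- **Use observed intervals only.** The comparison is then made among women who received pharmacological relief. Receipt happens after randomization and is something the intervention is meant to change, so the randomized comparison is lost.
- **Treat the absent intervals as missing and impute them.** This creates an epidural time for a woman who had no epidural.

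Either way NPI can understate a real delay, miss prevention, or move when only the length of labor changes. The last possibility is not remote: the Introduction cites evidence that TENS shortens active labor, and labor duration is itself a secondary outcome. The article presents NPI as its novel contribution, so a misleading result would carry weight.

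**Working it through.** **No figure to reproduce.** The article gives no expected NPI, standard deviation, epidural rate or power for NPI. Everything below rests on assumed inputs and shows direction and rough size only.

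**Step 1: how many women would lack an NPI.** The planned group size is 147 (Sample Size). If a fraction p receives an epidural, 147 × p have an interval and 147 × (1 − p) do not.

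| Assumed p | With NPI | Without NPI |
|---|---|---|
| 30% | 147 × 0.30 = 44 | 103 |
| 50% | 147 × 0.50 = 73.5 | 73.5 |
| 70% | 147 × 0.70 = 103 | 44 |

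**Step 2: what a recipient-only mean shows.** Assumed: log-normal labor, median 8 h, SD of the log 0.5; exponential time to epidural request, median 6 h in the reference arm; a start time granted to every arm. An epidural is observed if the request precedes delivery.

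| Scenario | Epidural rate | Mean NPI in recipients | Mean epidural-free time, all women |
|---|---|---|---|
| Reference | 60% | 3.9 h | 5.2 h |
| Delay, hazard ratio 0.6 | 44% | 4.5 h | 6.4 h |
| A random 40% of would-be recipients spared | 36% | 3.9 h | 6.8 h |
| Mainly late requesters spared | 37% | 2.4 h | 6.5 h |

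Under pure delay, recipients show 4.53 − 3.94 = 0.59 h, while all women gain 6.36 − 5.23 = 1.13 h. Under random prevention, recipients show no difference. When late requesters are spared, the sign reverses.

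**Step 3: power and false signals.** Assumed: 150 per arm, control epidural hazard 0.18 per hour, log-normal labor with median 6 h and SD of the log 0.5, giving a control epidural rate of about 65%. Women are independent, with no LDU effect. A recipient-only t test is compared with a log-rank test on all women (delivery censored) and a chi-square test on the epidural rate. Repeated runs differ by a point or two.

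| Scenario | Recipient-only t test | Log-rank, all women | Epidural rate |
|---|---|---|---|
| Hazard ratio 0.7 | 14% | 66% | 55% |
| 25% never request an epidural | 5% | 84% | 83% |
| Labor shortened from 6 to 5 h, nothing else | 13% to 15% | 4% to 5% | 19% |

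**Step 4: range.** When the control epidural rate varies from 32% to 81%, power at a hazard ratio of 0.7 is 6% to 28% for the recipient-only t test and 37% to 77% for log-rank. With shorter labor alone, the t test rejects in 12% to 15% across runs.

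**The case against.** The strongest reply has four parts.

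- **Nothing says that women are dropped.** A reader might infer that the plan excludes women without an epidural. The article does not say so: it does not assign a test to NPI by name, and intention to treat with imputation points the other way. This stands. The recipient-only figures describe one of two routes. The other route, imputation, fails for a different reason.
- **Control women may have a usable start.** A reader might infer that they have none, or that they received nothing nonpharmacological. The documents do not support this. Table 1 starts the separate techniques at the onset of contractions, and Outcome Measures starts VAS recording at the onset of labor pain without restriction by arm. A common origin is available; the article does not tie NPI to it.
- **Prevention is measured elsewhere.** A reader might infer that the trial is blind to prevention. It is not: "Secondary outcomes included the interval from the NPI, the rate of epidural analgesia" shows a separate outcome covering every woman, and in Step 3 it detects prevention about as well as log-rank (83% against 84%). But it does not measure delay, and it too moves when labor shortens (19%).
- **Event definitions and censoring rules often sit in an analysis plan that is not shown.** This is fair for detail. It does not remove the mismatch between a stated purpose and the stated tests.

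**Conclusion.** The point holds for NPI as a secondary outcome. With the methods as stated, NPI either conditions on pharmacological relief or rests on imputed epidural times, so it cannot support the delay-or-prevention claim made for it.

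The size is illustrative. It depends on assumed epidural hazards, labor lengths and hazard ratios, and on treating women as independent, which flatters the log-rank powers in a trial with four LDUs. The pattern held across control epidural rates of 32% to 81%. One ambiguity remains: the Introduction counts nitrous oxide and intravenous opioids as pharmacological, while the Discussion ties NPI to epidural analgesia.

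Severity is should-fix. The primary VAS outcome and the sample size do not depend on NPI, and the epidural rate partly covers the gap, so a more severe rating is not supported.

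**What to change.** 1. Define NPI in all four arms as time to epidural from one common origin, for example the onset of regular contractions, or of labor pain, where VAS recording already starts. State how other pharmacological relief is counted.
2. Include every woman, with delivery without epidural as a competing event. Fit a cause-specific Cox model with delivery censored, and show the cumulative incidence of epidural by arm.
3. Adjust for LDU and period as fixed effects. Do not rely on sandwich errors clustered on only four LDUs, which are unreliable at that number.
4. Do not impute NPI for women who had no epidural.
5. Report recipient-only NPI as descriptive, beside the epidural rate. Read both with labor duration, since the epidural rate and the cumulative incidence also move when labor shortens.

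The cost is analysis-plan wording, plus a check that the origin, epidural and delivery times were recorded alike in every arm; the article says only that secondary outcomes other than the childbirth experience come from electronic records. The downside is that the result becomes a hazard ratio and a cumulative incidence rather than a mean interval. Results reports data collection complete and analysis in progress, so the change should be dated and, if arm-level results have been seen, labeled post hoc.
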